#### Brief Fatigue Inventory

It is an instrument developed to assess fatigue in cancer patients that consists of 10 items with a Likert-type scale that assesses fatigue experienced in the last 24 h from 0 (no fatigue) to 10 (worst fatigue imaginable). It also includes a scale to assess the degree to which fatigue has interfered with the patient’s daily life in the last 24 h, with a scale ranging from 0 (does not interfere) to 10 (completely interfered). The recommended cut-off points in cancer patients are: 1–3 (mild); 4–7 (moderate) and 8–10 (severe) (Chang et al., 2007). The scale has adequate psychometric properties in its original version (α = 0.96) and in its adaptation to Spanish (α = 0.97) (Mendoza et al., 1999; Lorca et al., 2016).

#### Insomnia Severity Index

This instrument is designed to assess the severity of sleep onset, sleep maintenance and early morning awakening problems along with satisfaction with sleep pattern, interference with daily functioning, noticeability of impairment attributed to the sleep problem by others, and degree of distress or concern related with the sleep problem through 7 items that are scored on a scale from 0 (not at all) to 4 (very severe/very dissatisfied/very much). The sum of the scores given by the subject to the different items results in a total score that ranges from 0 to 28. The recommended cut-off points are as follows: 0–7 (absence of clinical insomnia), 8–14 (subclinical insomnia), 15–21 (moderate clinical insomnia), and 22–28 (severe clinical insomnia). The psychometric properties of the instrument are adequate in its original version (α = 0.91) and in its adaptation to Spanish (α = 0.82) (Bastien et al., 2001; Fernández-Mendoza et al., 2012).

#### Post-traumatic Growth Inventory-Short Version

It is an instrument designed to evaluate the positive change that people who are subjected to a traumatic event may experience, using 10 items that respond to a Likert-type scale from 0 (I have not experienced that change) to 5 (I have experienced that change to a great extent), with higher scores showing greater positive change. The instrument has good psychometric properties in its original version (α = 0.90) and in its adaptation to Spanish (α = 0.83) (Tedeschi and Calhoun, 1996; Castro et al., 2015).

*EORTC QLQ C-30 (version 3).* This is an instrument developed to assess the quality of life in cancer patients using 30 questions that refer to the quality of life experienced by the patient during the last week. The first 28 items include questions about different symptoms and are answered on a scale that ranges from 1 (not at all) to 4 (a lot), while the last two ask patients about the perception of their global health and quality of life in a scale from 1 (terrible) to 7 (excellent). The different items are grouped into the functional subscale (physical/role/emotional/cognitive/social and global) and the symptom subscale (fatigue/nausea and vomiting/dyspnea/sleep problems/loss of appetite/constipation/diarrhea and financial impact). This instrument has been developed to be applied in cancer patients obtaining good psychometric properties in its version in Spanish (α > 0.70) (Aaronson et al., 1993).

In addition to the scales and questionnaires described above, a specific scale will be included to consult the participants about their satisfaction with the intervention received in the present study. In order to ensure that participants will complete the follow up assessments, the psychotherapists will contact by phone to the participants monthly after the intervention ends to remind them the necessity to complete the planned assessments.

### Data Management

To ensure the anonymity, a code number will be assigned to each participant. Participants’ responses to the sociodemographic data and questionnaires will be collected on paper and kept in a locked filing cabinet during and after the trial ends. The mobile application that will be used in this project does not collect personal information from the end user, nor from the terminal on which it is installed, nor from the history or content of its internal memory. The purpose of the application is an additional aid to therapeutic treatment, offering a series of activities and exercises, from which only information is collected on whether they have been performed or not. Access to the application is not available for all users, although it will be hosted in the main stores in the market. The user/patient enters by identifying themselves with a tracking code that only their therapist knows, as otherwise they could not be tracked effectively. The information that can be stored (never of a personal nature) will be synchronized with a MySQL database hosted on the servers of the University of Córdoba, which have high security and stability standards. Access directly from mobile terminals to the database is not allowed, precisely in compliance with rigorous security protocols, so it is done through web services executed on the machine itself, within the secure environment of the University of Córdoba.

### Statistical Methods

Data will be analyzed following the intention to treat (ITT) and per protocol approaches. First, ANOVA or chi-square will be performed to compare the sociodemographic variables and the outcome measures at baseline (T0). Second, to examine the longitudinal changes over time (baseline, post-treatment and follow-ups) and the differences between groups in the variables under study, we will use mixed linear models, since these models are more precise than the repeated measures ANOVA (Gueorguieva and Krystal, 2004). In ITT analysis (all randomized patients are included in the analysis), incomplete or missing data will be considered using the maximum likelihood estimation method. In addition, the effect sizes will be calculated by Cohen’s *d* (bias corrected) (Hedges, 1981) as a measure of the differences between the Standardized Mean Changes (SMC) (T0-T1; T0-T2; T0-T3) of the respective groups (Becker, 1988). We will use the formula *d* = *c* ⋅ ([*M*_*pre*_ –*M*_*post*_]/*SD*_*pre*_) to obtain the SMC, where *c* is the bias correction factor, *M*_*pre*_ and *M*_*post*_ are the means of the pre–test and post–test scores, respectively, and *SD*_*pre*_ is the pre–test standard deviation score (Morris and DeShon, 2002). The SMC will be calculated for each group, providing the *d* index of the general effect size from the differences between them (Face-to-face ACT group vs. Face-to-face ACT group + App; Face-to-face ACT group vs. Waitlist group; Face-to-face ACT group + App vs. Waitlist group). Once the analyses have been performed, summary tables will be displayed for all the planned evaluations: pre-treatment (T0), post-treatment (T1), follow-up at 3 months (T2) and follow-up at 6 months (T3). The results will show frequencies and descriptive statistics (the mean, standard deviation and percentages) to summarize the characteristics of both the total sample and the participants that make up each of the three groups. Finally, the results of the study will be shown in accordance with the 2010 statement of the Consolidated Standards of Reporting Trials (CONSORT) (Moher et al., 2010; Schulz et al., 2010).

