### Sample Size

To determine the optimal sample size, we considered the effect sizes in psychological flexibility obtained in previous works by other authors. A recent meta-analysis (Chunxiao et al., 2020) examined the effect of ACT (including face-to-face and internet-based modalities) on psychological flexibility compared with treatment as usual or waitlist in cancer patients. The results showed a moderate effect size (Hedges’ *g*) of 0.58 at post-treatment. Taking into account these results, a medium effect size of 0.5 (Cohen’s *d*) has been assumed to detect differences between the interventions and waitlist group. Since no software to determine sample size for linear mixed model analyses was available, we used the *f* index of G*Power. Therefore, an effect size of 0.25 (index f) is assumed, equivalent to Cohen’s *d* = 0.5. Thus, with a statistical power of 0.80, an alpha level of 0.05 and a correlation between repeated measures of 0.5, a total sample of 102 participants is required (34 subjects in each group). In order to control the lack of participants during the intervention and evaluation process, based on a previous study (Arch and Mitchell, 2016) we assume a dropout rate of 10%. Consequently, we require to include 112 participants in our study (38 participants per group).

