### Recruitment and Assignment to Interventions

Participants will be recruited at the Reina Sofia University Hospital in Córdoba (Spain). The oncology and nursing team will approach to possible participants following the inclusion and exclusion criteria of the protocol during their visits. Eligible participants will sign an informed consent before randomization. Participants will be randomly allocated to one of the three conditions of the study (face-to-face ACT + app/face-to-face ACT/waitlist group) in a ratio of 1:1:1 using computer-generated sets of numbers^1^ and stratified by cancer type (breast/lung/colorectal). Group assignment will be provided to the trial research team in closed opaque envelopes. Randomization and allocation concealment will be carried out by trial independent research staff.

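### If T0 group means are left free in the mixed model, as the wording implies, each single-visit contrast carries one third more variance than a baseline-adjusted one at the plan's own correlation of 0.5

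*Protocol article*

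**What the plan says.** Three statements in Statistical Methods bear on baseline.

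- The mixed linear models are to be used "to examine the longitudinal changes over time (baseline, post-treatment and follow-ups) and the differences between groups in the variables under study". Baseline is thus a level of time, alongside T1, T2 and T3. The article does not list the fixed effects or covariates, and does not say whether the arms share a common T0 mean.
- Effect sizes are defined explicitly. For each arm, a bias-corrected standardized mean change from T0 is computed for T0–T1, T0–T2 and T0–T3. Effects are the differences between arms in these changes, for all three pairs of arms. No baseline adjustment enters the formula.
- Before modelling, "ANOVA or chi-square will be performed to compare the sociodemographic variables and the outcome measures at baseline (T0"). No use of the results is stated.

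Sample Size fixes the inputs needed here: "with a statistical power of 0.80, an alpha level of 0.05 and a correlation between repeated measures of 0.5". It also says that "a total sample of 102 participants is required (34 subjects in each group"). The assumed effect is d = 0.5 for each intervention against waitlist.

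Recruitment and Assignment to Interventions says that randomization is "stratified by cancer type (breast/lung/colorectal").

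**The concern.** In a randomized trial with T0 measured before allocation, the arms share one T0 population mean. An analysis that estimates a separate T0 mean for each arm and subtracts it carries the chance T0 imbalance into the treatment contrast. At moderate correlation between visits, subtracting the whole T0 difference over-corrects. Regression on T0, or a common T0 mean, removes only the part that T0 predicts.

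The stake is precision. The three hypotheses in the Introduction are pairwise comparisons at T1, T2 and T3. The planned 102 comes from an overall F test across three arms (shown in the working), so a pairwise contrast at one visit has less than 80% power under the plan's own assumptions. An analysis that recovers power from measurements already taken is worth having. Baseline significance tests do not help, because they adjust nothing.

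**Working it through.** **Inputs.** From Sample Size: r = 0.5, alpha 0.05, d = 0.5 (f = 0.25), 34 per arm. From Study Design and Settings: three arms, four times. Assumed here: equal variance (σ² = 1) and equal correlation at all times, two-sided tests, complete data.

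**1. The plan's own figure.** For the between-groups F test in a repeated-measures ANOVA with m = 4 times, the noncentrality is N f² m / (1 + (m − 1)r). At N = 102 this is 102 × 0.0625 × 4 / (1 + 3 × 0.5) = 25.5 / 2.5 = 10.2. With 2 and 99 degrees of freedom, power is 0.811. The smallest N reaching 0.80 is 100, which becomes 102 in multiples of three. The stated total reproduces as an overall test, not as a pairwise contrast.

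**2. Variance per arm of a single-visit contrast.**

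- Change from T0: 2(1 − r) = 2 × 0.5 = 1.00.
- Baseline-adjusted: 1 − r² = 1 − 0.25 = 0.75.
- The excess is 2(1 − r) − (1 − r²) = (1 − r)² = 0.25, which is the chance T0 imbalance carried into the contrast.
- Relative to the change score, the variance reduction is 1 − 0.75/1.00 = 25%. The standard error falls by 1 − √0.75 = 13.4%.
- Equivalent sample: 1/0.75 = 1.33, or one third more patients.
- At r = 0.5 the simple T1 difference also has variance 1.00, so the 25% is the same against either unadjusted contrast.

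**3. Check in the full model.** Generalized least squares for three arms, four times and 34 per arm gives, for a pairwise T1 contrast:

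- T0 means free: 0.0588 (= 2 × 1.00/34).
- T0 as an outcome with one common mean: 0.0441 (= 2 × 0.75/34).

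The second equals the covariate-adjusted result. The loss therefore comes from leaving the T0 means free, not from having T0 among the outcomes.

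**4. Pairwise power at T1**, d = 0.5, 34 per arm, t test with 66 degrees of freedom. At r = 0.5 the noncentralities are 0.5/√0.0588 = 2.06 and 0.5/√0.0441 = 2.38.

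| r | Change variance | Adjusted variance | Reduction | Power, change | Power, adjusted |
|---|---|---|---|---|---|
| 0.3 | 1.40 | 0.91 | 35% | 0.404 | 0.567 |
| 0.5 (plan) | 1.00 | 0.75 | 25% | 0.529 | 0.650 |
| 0.7 | 0.60 | 0.51 | 15% | 0.746 | 0.812 |

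At r = 0.5, 80% pairwise power needs about 63 per arm unadjusted and 48 adjusted (normal approximation).

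**5. Cancer type.** The article gives no figure for the variance it explains. Suppose, as an illustration, that it explains 10% of total variance, constant over time, at r = 0.5. A constant effect cancels from a change score, so a main effect for type does not alter that contrast. After baseline adjustment the residual variance goes from 0.75 to 0.9 − 0.4²/0.9 = 0.722, a reduction of about 4%. If type instead explained 5–10% of the variance left after baseline adjustment (also assumed), power would go from 0.650 to 0.672–0.696.

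**The case against.** The strongest reply is that much of this rests on what a condensed article does not say. The article names mixed linear models and lists baseline among the times, but gives no fixed effects, covariates or T0 constraint. Those are commonly left to an analysis plan, and none is shown. If the T0 means are constrained equal there, the loss in the model is zero. That stands, and it makes the model figure conditional. It does not reach the effect sizes, which are fully defined and are unadjusted change differences. Nor does a planned comparison of T0 outcome means between arms sit naturally with a model that sets those means equal.

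A reader might infer that the plan ignores its stratification factor and that its standard errors are therefore too large. The article does not support this: it neither includes nor excludes cancer type as a model term, and a time-constant type effect cancels from a change contrast anyway. The Discussion says only that differing diagnoses and treatments may influence results, with no size.

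A reader might also take the baseline tests as the chosen substitute for adjustment. The article does not say so. They are uninformative under randomization, but do not alter the treatment estimate.

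**Conclusion.** The point holds as one of efficiency. If the T0 means are free, a single-visit pairwise contrast has variance 1.00 per arm where 0.75 is available at r = 0.5: 25% in variance, about 13% in standard error. T1 power at d = 0.5 with 34 per arm would rise from about 0.53 to 0.65.

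The size depends on r (a 35% reduction at 0.3, 15% at 0.7), on equal variances and correlations, and on complete data. It applies to one visit at a time. The d = 0.5 is the plan's assumption for an intervention against waitlist; the article gives no corresponding figure for the two ACT arms against each other.

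Three stronger readings go too far. Treating T0 as an outcome does not in itself cost precision. None of the 25% comes from cancer type. And the comparison is not biased: chance imbalance at T0 averages out over randomizations, and what remains is extra variance. This should be changed, but it does not invalidate the planned analysis.

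**What to change.** In Statistical Methods, state the model in one of two equivalent forms:

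- T1, T2 and T3 as outcomes, with T0 value, T0-by-visit, arm, visit and arm-by-visit as fixed effects; or
- T0 to T3 as outcomes, with one T0 mean common to the three arms and arm differences from T1 onward.

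Take the reported between-group effects from this model, standardized if wanted, in place of raw differences in standardized mean change. Show T0 by arm descriptively and drop the baseline significance tests.

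As a secondary change, add cancer type as a fixed effect, since it is the randomization stratum. The reason is consistency with the design; no particular gain in power should be promised.

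The cost is a few sentences of wording. No new data, visits or patients are needed.

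### Standardising each arm's change by its own baseline SD adds avoidable noise to the between-arm d, mainly for ACT + app versus ACT; one pooled T0 SD would remove it

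*Protocol article*

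**What the plan says.** Statistical Methods tests change over time and group differences with linear mixed models: "we will use mixed linear models, since these models are more precise than the repeated measures ANOVA". In addition, it plans a bias-corrected d "as a measure of the differences between the Standardized Mean Changes (SMC") for T0–T1, T0–T2 and T0–T3. The standardised mean change is c × (M_pre − M_post) / SD_pre, where SD_pre "is the pre–test standard deviation score". The order of operations is then fixed: "The SMC will be calculated for each group", and the d index follows from the differences between groups, for all three pairwise comparisons. No SD common to the arms is mentioned. On a plain reading, each arm's change is scaled by that arm's own baseline SD before the subtraction.

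Study Design and Settings places T0 before randomisation and allocates 1:1:1. Sample Size gives 34 evaluable and 38 enrolled patients per group.

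**The concern.** Patients are randomised from one population after the baseline measurement, so the three arms have one true T0 SD for each scale. The plan estimates it three times, each time from about a third of the data, and subtracts quantities that have been divided by different numbers. Two arms with identical raw improvement then show a non-zero d whenever their sample SDs happen to differ.

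The size of this distortion depends on the change that the two arms share. It is therefore largest for ACT + app versus ACT, the contrast of Hypothesis 1. Both arms receive the same eight-session programme and both are expected to improve, so any increment due to the app may be modest and a stray 0.10 in d is not trivial beside it. The same T0 SDs also enter d at T1, T2 and T3, so a chance difference in baseline spread carries through all three visits of a scale. This d is the only standardised effect measure that Statistical Methods describes.

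**Working it through.** **Inputs from the protocol article.** 34 evaluable or 38 enrolled per arm, and correlation between repeated measures r = 0.5 (Sample Size: "with a statistical power of 0.80, an alpha level of 0.05 and a correlation between repeated measures of 0.5"). **Assumptions.** Normal scores; equal true SDs (set to 1) at T0 and at follow-up; within-arm changes of 0, 0.5 or 0.8 SD, because the article gives no within-arm change; r = 0.3 and 0.7 as a range around 0.5; c = 1 − 3/(4·df − 1).

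**The plan's own figure.** The article gives no value for d or its variance, but the sample size behind n and r can be checked. In a repeated-measures between-factor F test with f = 0.25, 4 visits and r = 0.5, λ = 0.25² × 102 × 4 / (1 + 3 × 0.5) = 10.2 with df 2 and 99. Power is 0.811 (0.798 at N = 99), so "a total sample of 102 participants is required (34 subjects in each group") reproduces.

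**Step 1: how far two baseline SDs differ by chance.** The squared ratio of two sample SDs follows F(n−1, n−1).

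| Larger SD / smaller SD exceeds | n = 34 | n = 38 |
|---|---|---|
| 1.10 | 59% | 57% |
| 1.20 | 30% | 27% |
| 1.22 | 25% | 23% |

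**Step 2: what that does to d in one trial.** Take sample SDs of 0.9 and 1.1, a ratio of 1.22. An identical raw change of 0.5 gives 0.5/0.9 − 0.5/1.1 = 0.556 − 0.455 = 0.10. An identical change of 0.8 gives 0.889 − 0.727 = 0.16. The correction c is 0.977 at n = 34 and hardly alters these values. With one common divisor, d is exactly 0 in both cases.

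**Step 3: variance over repeated trials.** With a shared change δ, a first-order approximation is:

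- own-arm SDs: 4(1 − r)/n + δ²/(n − 1)
- common SD: 4(1 − r)/n

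At n = 34, r = 0.5 and δ = 0.5, this gives 0.0588 + 0.0076 = 0.0664 against 0.0588, a ratio of 1.13. The extra term does not depend on r, so the relative loss grows with r and with δ². Simulation (200,000 trials per row, n = 34 per arm, common SD pooled over three arms) gives:

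| Changes in the two arms | r | SE of d, own-arm | SE of d, pooled | Variance ratio |
|---|---|---|---|---|
| 0.5 and 0.5 | 0.3 | 0.302 | 0.287 | 1.11 |
| 0.5 and 0.5 | 0.5 | 0.261 | 0.243 | 1.15 |
| 0.5 and 0.5 | 0.7 | 0.210 | 0.188 | 1.24 |
| 0.5 and 0 | 0.3 | 0.296 | 0.290 | 1.04 |
| 0.5 and 0 | 0.5 | 0.253 | 0.246 | 1.06 |
| 0.5 and 0 | 0.7 | 0.199 | 0.191 | 1.09 |
| 0.8 and 0.8 | 0.5 | 0.284 | 0.243 | 1.36 |

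With 38 per arm the ratios are almost the same (1.15 for 0.5 and 0.5 at r = 0.5). In standard-error terms, 0.261/0.243 is about 7% wider and 0.253/0.246 about 3% wider.

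**Step 4: bias.** In the same simulations, the mean of the own-arm d is 0.00 when both arms change equally and 0.50 when the true difference is 0.5.

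**The case against.** The strongest reply is that this is a published and cited estimator, it is unbiased, and nothing inferential depends on it. Much of that stands. The mixed models supply the tests; no sample size, hypothesis test or decision rule uses d. A stray 0.10 is about 0.4 of one standard error of d (0.10/0.261). For active versus an unchanged waitlist the loss is only 2–4% in standard error. Planned group means and SDs would let a reader recompute d with a pooled SD. The 0.8 SD row rests on a shared change that the article does not give, so it shows direction rather than an expected size.

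Three stronger readings are tempting, and the document supports none of them:

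- A reader might infer that d is systematically spurious. Step 4 shows that it is not: the departure is noise in the single trial.
- A reader might infer that the significance tests are compromised. They do not use d.
- A reader might infer that, with dropout, d will be built from raw means of different patients at T0 and later and so will contradict the tested contrast. The article refers only to pre-test and post-test means and does not say whether these are raw or model-estimated. That detail may sit in the full plan.

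What the reply does not remove is that the article fixes a formula, and that a more precise one is available from the same data at no cost. If the investigators already intend SD_pre to be pooled, the point reduces to saying so, because the present wording reads otherwise.

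**Conclusion.** The point holds as a free improvement in precision, not as an error that threatens the trial's conclusions. With 34 to 38 patients per arm and equal true baseline SDs, own-arm scaling makes the variance of d about 11–24% larger for r = 0.3–0.7 when both arms change by 0.5 SD. At the protocol's r = 0.5 the figure is about 15%, or about 7% in standard error. For a change of 0.5 SD against none, the excess is about 4–9% in variance. In roughly a quarter of trials, two arms with the same 0.5 SD improvement would differ by about 0.10 or more in d through baseline spread alone.

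The practical relevance is concentrated in ACT + app versus ACT. The figures rest on normal scores and on assumed within-arm changes; if both arms change little, the loss nearly vanishes, and if both change by more than 0.5 SD, it grows.

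**What to change.** Replace the arm-specific divisor with one common SD for each scale: the T0 SD pooled over the three arms. Use it for all three contrasts and all three post-baseline visits, and base the small-sample correction on the pooled degrees of freedom (3 × 34 − 3 = 99, or 3 × 38 − 3 = 111). The numerator is the between-arm difference in change at that visit. Taking it from the mixed model is preferable, because d then describes the contrast that is tested, but the pooled SD alone removes the problem described here.

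The cost is one sentence of analysis wording. All inputs are already collected, and the sample size and the tests do not change.
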